### Cost-effectiveness analysis

For both strategies, costs in the stimulation phase and effectiveness will be calculated from the complete cases. At the time of pregnancy testing, participants will be questioned to determine the costs of drugs in the stimulation phase. Furthermore, ongoing pregnancy achieved after natural conception or via conception other than a regular IVF or ICSI treatment is not included in the analysis.

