#### Oocyte retrieval, in vitro fertilization, and embryo transfer

Transvaginal ultrasound-guided oocyte retrieval will be performed 36 h later. Retrieved oocytes are fertilized by either IVF or ICSI, depending on sperm quality. For participants receiving fresh embryo transfer (ET), transfer is performed with two of the highest quality embryos at the cleavage stage 3 days after oocyte retrieval. Luteal-phase support with vaginal progesterone gel (Crinone, Merck Serono) at a dose of 90 mg daily and oral dydrogesterone (Duphaston, Abbott) at a dose of 10 mg twice daily is started after oocyte retrieval and continued until the day of hCG testing. If pregnancy is achieved, luteal phase support will be continued until 10 weeks’ gestation. Frozen ET will be taken if patients are at risk of OHSS; have an unfavorable endometrium (endometrial thickness of ≤ 6 mm or ≥ 16 mm, cavity fluid, or endometrial polyps); or have a P concentration of ≥ 1.5 ng/mL on the day of hCG trigger. For frozen ET, the endometrium is prepared using either a natural cycle regimen or an artificial cycle regimen based on the physician’s decision. For the natural cycle regimen, luteal phase support is started from the ovulation day with oral dydrogesterone (10 mg twice daily). For the artificial cycle regimen, the endometrium is prepared with oral estradiol valerate at a dose of 6–8 mg daily which will be started on days 3–5 of the menstrual cycle. Vaginal progesterone gel (90 mg daily) and oral dydrogesterone (10 mg twice daily) are added when the endometrium thickness reaches 8 mm. If pregnancy is achieved, luteal phase support will be continued until 10 weeks’ gestation.

Concomitant treatments such as traditional Chinese medicine and acupuncture are not permitted during the trial.

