### Outcome measures

The primary outcome will be the cumulative ongoing pregnancy rate resulting from one ART aspiration cycle, including fresh and FET cycles. Ongoing pregnancy is defined by the presence of a gestational sac with a fetal heartbeat after 12 weeks of gestation. The cycle in which no oocytes are retrieved or no embryo is available for transfer will be considered as not getting pregnant. Secondary outcomes will be high-quality embryo rate, clinical pregnancy rate, severe OHSS rate, and cancelation rate. Moreover, differences in cost-effectiveness and adverse events will be evaluated. Typically, a high-quality embryo is defined as an embryo with 7–10 cells and ≤ 25% fragmentation developed from 2PN embryos on day 3 after oocyte aspiration. The clinical pregnancy rate is defined as the presence of a gestational sac at 6–7 weeks of gestation when visualized by transvaginal ultrasound. Moderate OHSS is diagnosed when ovarian enlargement of > 5 cm and < 12 cm is observed and when ultrasonographic ascites are present with or without nausea, vomiting, and/or diarrhea. Severe OHSS is diagnosed when ovarian enlargement of ≥ 12 cm is observed and when there is clinical evidence of ascites and/or hydrothorax or breathing difficulties with or without hemoconcentration, severe hypoproteinemia, abnormal liver function, coagulation abnormalities, or diminished renal function.

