### Statistical analysis

Data analysis of this trial will follow the intention-to-treat principle, including a preliminary comparison of all randomized women in the two groups who did not drop out of the study. Differences between the groups will be compared between demographic variables and baseline information from before the start of the study. Continuous data with normal distribution will be estimated using a two-sample *t*-test, and the Mann-Whitney *U* test will be used for non-normally distributed data. Categorical data will be represented as frequency and percentage, and the differences in these variables will be assessed by the chi-square test or Fisher’s exact test. We will also compute the unadjusted risk ratio (RR) and its 95% confidence interval (CI). This test for non-inferiority will only be performed for the primary outcome; all other secondary outcomes will be tests of superiority. The primary outcome—cumulative ongoing pregnancy rate per cycle in women with PCOS in the control arm—was 80% in our center. Considering that a non-inferiority threshold should retain 80% of the clinical effect of a control treatment, the minimum clinical difference should be 16%. Noninferiority is declared if the upper limit of the two-sided 95% CI for the cumulative ongoing pregnancy rate in the study group does not exceed a relative margin of 16%, equivalent to a two-sided test with an *α* value of 2.5%. A two-sided *α* value of 0.05 is used for superiority testing.

In case of missing values of baseline characteristics, we will analyze them by excluding the missing values, then assign the missing values multiple times, and conduct subsequent analyses to estimate the robustness of the results. For follow-up loss and protocol violation, we will attempt sensitivity analysis to explore the influence of these factors on the trial results.

The flow chart of this study is given in Fig. 1. A schedule of enrollment, interventions, and assessment is provided in the Standard Protocol Items: Recommendations for Interventional Trials (SPIRIT) figure (Fig. 2), and the SPIRIT reporting guidelines are used as shown in Additional file 1 [14].

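### Cost-effectiveness rests on complete cases with drug costs asked only at the pregnancy test, so women who never reach a test probably fall out, and the cost window is shorter than the likely effect window

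*Protocol article*

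**What the plan says.** The section Cost-effectiveness analysis fixes three things.

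- Analysis set and cost scope: "costs in the stimulation phase and effectiveness will be calculated from the complete cases". The term complete cases is not defined.
- Source and time of the cost data: "At the time of pregnancy testing, participants will be questioned to determine the costs of drugs in the stimulation phase". No other collection point or source is named. Data collection adds only that economic outcomes are entered on a case report form.
- Which pregnancies are left out: "ongoing pregnancy achieved after natural conception or via conception other than a regular IVF or ICSI treatment is not included in the analysis". Frozen-transfer pregnancies are not among the exclusions, and effectiveness is not otherwise defined there.

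Outcome measures defines the primary outcome as the "cumulative ongoing pregnancy rate resulting from one ART aspiration cycle, including fresh and FET cycles" and adds: "The cycle in which no oocytes are retrieved or no embryo is available for transfer will be considered as not getting pregnant".

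Frozen transfer is part of planned care: "Frozen ET will be taken if patients are at risk of OHSS". The same section lists endometrial and progesterone reasons as well. It also describes preparation and luteal-support drugs that are given after stimulation has ended.

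**The concern.** A pregnancy test follows a transfer. A woman who has no transfer has no scheduled test, and so no stated occasion on which her drug costs would be asked. She used stimulation drugs and did not become pregnant. If she is missing from the economic set, her failure leaves the effectiveness denominator and her spending leaves the cost total.

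The loss need not be equal in the two arms. The arms differ in when and whether antagonist is given, and Data monitoring and safety gives a high cancellation rate from premature LH surge as its example of harm. If that harm occurred in one arm, it would remove failures from that arm's economic set and make the arm look more cost-effective.

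There is also a question of time window. If effectiveness is the cumulative rate, pregnancies from frozen transfers count while the drugs and procedures that produced them do not.

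The Abstract names cost-efficiency as a secondary outcome, and the Background gives cost-effectiveness as part of the trial's aim. In a non-inferiority trial of a regimen that may use less drug, cost is a main argument for adopting it.

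**Working it through.** The economic section states no figure to reproduce. The check is first of the text, then of the possible size.

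**1. Who has a cost record, following the text**

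| Woman | Primary outcome | Stated occasion for cost data |
|---|---|---|
| Reaches a transfer and a pregnancy test | Pregnant or not | Yes |
| No oocytes, or no embryo | Not pregnant (stated) | None |
| Cancelled before retrieval | Not named separately; arguably covered by the no-oocyte rule | None |
| Deferred to frozen transfer | Cumulative result | Yes, but later after stimulation |

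Rows two and three are the selection on outcome.

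**2. Effect on the pregnancy rate**

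Inputs: p = 80% (control rate, Sample size calculation). e = share of randomised women left out, all of them failures. The documents give no value for e, so 2%, 5% and 10% are assumed.

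Complete-case rate = p / (1 − e)

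- e = 2%: 0.80 / 0.98 = 81.6%
- e = 5%: 0.80 / 0.95 = 84.2%
- e = 10%: 0.80 / 0.90 = 88.9%

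With p = 80%, failures are 20% of women. So e = 10% means that half of all failures never reached a test, which is the high end.

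**3. Effect on drug cost per pregnancy**

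Let included women cost C each and excluded women fC.

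- All randomised: C × [(1 − e) + e·f] / p
- Complete cases: C × (1 − e) / p
- Ratio: (1 − e) / [(1 − e) + e·f]

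| e | f = 1: ratio, understatement | f = 0.5: ratio, understatement |
|---|---|---|
| 2% | 0.98, 2% | 0.98/0.99 = 0.990, 1.0% |
| 5% | 0.95, 5% | 0.95/0.975 = 0.974, 2.6% |
| 10% | 0.90, 10% | 0.90/0.95 = 0.947, 5.3% |

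**4. Effect on the comparison**

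- Equal e and f in both arms: both costs per pregnancy are multiplied by the same factor, so their ratio is unchanged.
- 80% in both arms, e = 5% in control and 10% in the LH-based arm: 0.889 − 0.842 = +4.7 points where the true difference is 0.
- 80% against 76% with the same exclusions: 0.76/0.90 − 0.80/0.95 = 0.844 − 0.842 = +0.2 points where the true difference is −4.

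**5. Cost window**

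This is an illustration in which every input is assumed. Stimulation in the LH-based arm costs 0.90 of control, and one frozen transfer costs 0.2 to 0.4 of control stimulation. The stimulation-only cost ratio is 0.90.

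- One frozen transfer per woman in each arm: (0.90 + 0.2)/(1 + 0.2) = 0.917 to (0.90 + 0.4)/(1 + 0.4) = 0.929.
- 1.5 in the LH-based arm against 1.0 in control: (0.90 + 0.3)/1.2 = 1.00 to (0.90 + 0.6)/1.4 = 1.07.

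The omission therefore matters little if frozen-transfer use is equal and could matter a good deal if it is not. The article does not show that it differs.

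**The case against.** The strongest reply is that the exclusion is inferred. Complete cases could mean women not lost to follow-up. That would match the Statistical analysis section, which describes its comparison as "including a preliminary comparison of all randomized women in the two groups who did not drop out of the study". Women with no oocytes or no embryo have a known outcome, and Data collection commits the investigator to follow every randomised woman. On that reading failures stay in. This stands as a possible reading, but it does not supply a cost record for those women, because no other occasion for obtaining one is given.

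The cost scope is a declared choice. The Discussion speaks of the cost of drugs, and the arms differ by design in antagonist use. Severe OHSS and cancellation are reported separately, so differences there remain visible. This stands too: a full costing of laboratory work, frozen cycles and OHSS care would change the economic perspective, and leaving it out is not in itself an error.

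A reader might also infer that the plan expressly drops these women, that it expressly counts frozen-transfer pregnancies in the cost analysis, or that one arm gains a spurious 10% advantage. The documents support none of these as stated fact. The first two are likely readings of undefined terms. The third needs 10% exclusion in one arm, none in the other, and full drug cost for every excluded woman. Nor does the article say whether answers to the questioning are checked against records.

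An article may leave costing detail to a fuller document. Here, though, the analysis set, cost scope, source and timing are all written down, and they do not fit together.

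**Conclusion.** The point holds as a defect in how the economic analysis is specified. As written, the plan gives no cost record to women who never reach a pregnancy test, and it analyses complete cases. The economic set is then probably selected on outcome, unlike the primary outcome. Over assumed exclusions of 2% to 10%, drug cost per pregnancy is understated by 2% to 10% at full drug cost for the excluded women, or by about 1.0% to 5.3% at half cost. The ratio between arms is biased only if exclusion, or the drug cost of the excluded women, differs by arm. The article foresees such a difference for cancellation but does not quantify it.

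The mismatch of windows rests on reading effectiveness as the cumulative rate. That is the likeliest reading, given the primary outcome, the narrow list of excluded pregnancies, and the Background's account of the team's earlier trial in terms of the whole treatment cycle.

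Cost-effectiveness lies outside the non-inferiority test, so the primary conclusion does not change. The correction should be made because cost is a named objective.

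**What to change.** 1. Define the economic analysis set as all randomised women. Cancelled, no-oocyte and no-embryo cycles carry the stimulation drug cost that they incurred and zero effect.
2. Derive drug cost from recorded doses or dispensing records for every woman, rather than from questioning at the pregnancy test.
3. State that effectiveness is the cumulative ongoing pregnancy rate, if that is what is meant. Then either add frozen-cycle costs over the same window as a sensitivity analysis, or label the result throughout as stimulation-drug cost only.

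The cost is a modest records extract at one hospital and some added analysis. The article does not describe those records, so their availability has to be confirmed. More than 180 of the planned 216 women were already enrolled at the time of writing, so changing the interview alone would come too late for most of them. A records extract would not need new patient contact. Adding frozen-cycle costs is the larger piece of work, and labelling the result as stimulation-drug cost is the cheaper alternative.

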### Data collection

Data for both clinical and economic outcomes will be collected by using a standard case report form developed in the web-based data entry system. All data will be entered into the database twice by two different doctors at the termination of the study to prevent operational errors. Once a patient is enrolled or randomized, the investigator will make every reasonable effort to follow her for the entire study period. Cell phone numbers of the wife, husband, and another family member will all be recorded. The prespecified staff are responsible for the follow-up. During the trial, there will be several other methods to improve retention, such as scheduling appointments with the clinician and keeping in contact with the investigators through apps such as WeChat. The relevant description has been added to the manuscript.

### Data monitoring and safety

All data will be supervised by independent statisticians from Beijing Chao-Yang Hospital. All clinical research will be carried out as per the Good Clinical Practice (GCP) standards. The study site monitor will check the maintenance of trial-related source records, authenticity, and integrity of the data regularly to ensure adherence to the protocol, standard operating procedures, and applicable regulatory requirements. Adverse events (AEs) are defined as any undesirable event experienced by a subject during a clinical trial, regardless of whether the event is considered related to the intervention. Routine assessments for OHSS were performed on day 2 after oocyte retrieval in both groups. At all other times, OHSS will be evaluated and classified if symptoms are reported by the patient. A serious adverse event (SAE) is defined as any untoward medical occurrence or effect that results in death, is life-threatening (at the time of the event), requires hospitalization, prolongs an existing hospitalization, results in persistent or significant disability or incapacity, is a congenital anomaly or birth defect, and is a new event of the trial likely to affect the safety of the subjects such as an unexpected outcome of an adverse reaction. All AEs reported spontaneously by the subject or observed by the investigator or their staff will be recorded accurately in the eCRFs and will be followed up during the course of the AE until their resolution or for 2 weeks after the end of the trial. All SAEs will be reported to the investigators, discussed through a web-based AE reporting system, and will be reported to the Pharmaceuticals and Medical Devices Agency, if necessary. There will be an interim analysis. If the data show convincing evidence of harm, such as a high cancelation rate due to premature LH surge, the trial would be stopped by the investigators or the data monitoring committee.

Over the course of the trial, some tiny modifications, such as modification of the follow-up method from telephone to short message for some subjects, will not trigger a protocol amendment. However, protocol amendment will be performed if the most relevant and critical modifications that affect the trial design and data collection procedure occurred. A modified version, if applicable, will be submitted to the sponsor for funding, to the IRB for ethics approval, and to the data monitoring committee.

### Statistical analysis

Data analysis of this trial will follow the intention-to-treat principle, including a preliminary comparison of all randomized women in the two groups who did not drop out of the study. Differences between the groups will be compared between demographic variables and baseline information from before the start of the study. Continuous data with normal distribution will be estimated using a two-sample *t*-test, and the Mann-Whitney *U* test will be used for non-normally distributed data. Categorical data will be represented as frequency and percentage, and the differences in these variables will be assessed by the chi-square test or Fisher’s exact test. We will also compute the unadjusted risk ratio (RR) and its 95% confidence interval (CI). This test for non-inferiority will only be performed for the primary outcome; all other secondary outcomes will be tests of superiority. The primary outcome—cumulative ongoing pregnancy rate per cycle in women with PCOS in the control arm—was 80% in our center. Considering that a non-inferiority threshold should retain 80% of the clinical effect of a control treatment, the minimum clinical difference should be 16%. Noninferiority is declared if the upper limit of the two-sided 95% CI for the cumulative ongoing pregnancy rate in the study group does not exceed a relative margin of 16%, equivalent to a two-sided test with an *α* value of 2.5%. A two-sided *α* value of 0.05 is used for superiority testing.

In case of missing values of baseline characteristics, we will analyze them by excluding the missing values, then assign the missing values multiple times, and conduct subsequent analyses to estimate the robustness of the results. For follow-up loss and protocol violation, we will attempt sensitivity analysis to explore the influence of these factors on the trial results.

The flow chart of this study is given in Fig. 1. A schedule of enrollment, interventions, and assessment is provided in the Standard Protocol Items: Recommendations for Interventional Trials (SPIRIT) figure (Fig. 2), and the SPIRIT reporting guidelines are used as shown in Additional file 1 [14].

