### Randomization and blinding

Included patients participated in no more than two treatment cycles. Women meeting the inclusion criteria will be randomized according to an online central randomization database (www.medresman.org) in a 1:1 ratio on the day of stimulation. The online sequence is generated and input into the online central randomization system by the staff members who are not involved in enrolling subjects. It is not accessible to any investigators or study coordinators. If a subject fulfills the enrollment criteria, the authorized investigator will log in to the password-protected account to get the assignment. After randomization, patients will be blinded to group allocation and randomly assigned to one of two groups: the control group (traditional flexible GnRH antagonist protocol) or the experimental group (LH-based flexible GnRH antagonist protocol). The nature of the treatment interventions precludes blinding of treating physicians. However, this study will be blinded to embryologists, laboratory technicians, and nurses who conduct follow-ups until the completion of the statistical analysis of this study.

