### Sample size calculation

According to the literature and data from our center, the cumulative ongoing pregnancy rate per cycle in women with PCOS in the control arm was around 80%. Considering that a non-inferiority threshold should retain 80% of the clinical effect of a control treatment, a minimum clinical difference of 16% (two-sided: *α*, 2.5%; *β*, 20%) and a total of 196 patients were needed. Considering a possible withdrawal rate of 10%, the total number of patients required will be 216.

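### High-quality embryo rate is defined per embryo while women are randomised, and the plan's rule for categorical outcomes makes no allowance for several embryos from one woman

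*Protocol article*

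**What the plan says.** Under Randomization and blinding, women are allocated "in a 1:1 ratio on the day of stimulation". The randomised unit is therefore the woman.

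Under Outcome measures: "Secondary outcomes will be high-quality embryo rate, clinical pregnancy rate, severe OHSS rate, and cancelation rate". The first of these rests on a property of the single embryo: "a high-quality embryo is defined as an embryo with 7–10 cells and ≤ 25% fragmentation developed from 2PN embryos on day 3" after aspiration. No denominator is given for the rate.

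The Statistical analysis section assigns tests by type of data, not by outcome. Normally distributed continuous data go to a two-sample t-test, and "the Mann-Whitney *U* test will be used for non-normally distributed data". Categorical data are shown as frequency and percentage, and "the differences in these variables will be assessed by the chi-square test or Fisher’s exact test". An unadjusted risk ratio with its 95% CI is added. Secondary outcomes are tested for superiority, where a two-sided alpha "value of 0.05 is used for superiority testing". The section has no provision for correlated observations.

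**The concern.** Whether an embryo is of high quality is a yes-or-no property, and a rate of such embryos is most readily shown as a frequency and percentage. On that reading the outcome falls under the categorical rule, with embryos as the counted units. Chi-square, Fisher's exact test and the usual CI for a risk ratio all treat the counted units as independent. Embryos from one woman share her oocytes, her stimulation course and normally the same sperm source, so their quality is likely to be positively correlated. Pooling them counts more information than the trial holds.

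At stake is the reliability of one formally tested secondary outcome. The Background argues that LH activity matters for follicular development and oocyte maturation. Of the listed secondary outcomes, embryo quality lies closest to that mechanism, so a p-value below 0.05 could be read as support for the new protocol.

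**Working it through.** **The plan's own figure.** The article gives no figure for high-quality embryo rate. Its only calculation is for the primary outcome: control rate 80%, margin 16 percentage points, z = 1.96 and power 80%. This gives 2 × 0.80 × 0.20 × (1.96 + 0.84)² / 0.16² = 98.1 per arm, or 196.2 in total, which matches the stated 196. Adding 10% gives 196 × 1.10 = 215.6, the stated 216. This calculation uses one binary result per woman, so correlation between embryos does not enter it.

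**Inputs for the check**
- Randomised unit: the woman (Randomization and blinding).
- Unit in which the event is defined: the embryo (Outcome measures).
- Nominal two-sided alpha: 0.05 (Statistical analysis).
- Embryos per woman, m: not in the article; assumed 6 to 10.
- Within-woman correlation of embryo quality, ICC: not in the article; assumed 0.1 to 0.3.

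**Formulas.** With equal numbers of embryos per woman, the variance of a pooled rate is inflated by the design effect DE = 1 + (m − 1) × ICC. The naive standard error is too small by the factor √DE. The true type I error of the naive test is 2 × [1 − Φ(1.96/√DE)].

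| m | ICC | DE | √DE | True type I error |
|---|---|---|---|---|
| 6 | 0.1 | 1 + 5 × 0.1 = 1.5 | 1.22 | 11.0% |
| 10 | 0.1 | 1 + 9 × 0.1 = 1.9 | 1.38 | 15.5% |
| 10 | 0.2 | 1 + 9 × 0.2 = 2.8 | 1.67 | 24.1% |
| 10 | 0.3 | 1 + 9 × 0.3 = 3.7 | 1.92 | 30.8% |

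Over the assumed range the nominal 5% becomes about 11% to 31%, and the CI should be 1.2 to 1.9 times wider.

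**Wider assumptions.** At m = 5 and ICC = 0.05, DE is 1.2 and the error 7.4%. At m = 15 and ICC = 0.30, DE is 5.2, the error 39.0% and the CI factor 2.28. The size moves a great deal with the assumptions, but the direction does not.

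**Simulation under no difference between arms.** Settings: 98 women per arm, 4000 runs per setting, beta-binomial embryo quality with an assumed rate of 40%, unequal embryo counts with mean 5, 8 or 10, and ICC 0.05, 0.1 or 0.2. Rejection rates at nominal 5%:
- Pooled embryos, chi-square type test: 8.6% to 28.3%.
- t-test on each woman's own proportion: 4.4% to 5.4%.
- Pooled rate with variance clustered on woman: 4.6% to 5.7%.

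Both woman-level analyses hold the nominal level, and the pooled test does not in any setting.

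**The case against.** The strongest reply is that the article does not prescribe the faulty analysis. A reader might infer that the plan tests pooled embryos by chi-square. The text does not say so: tests are assigned by data type, this outcome is not named, and no denominator is given. The same section frames the analysis as a comparison of randomised women. With the woman as the unit, the outcome is a proportion for each woman, which is continuous and falls under the t-test or Mann-Whitney rule, and the simulation shows that this is valid. The article also condenses a fuller protocol, and a statistical analysis plan that is not shown may settle the matter.

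All of this stands, and it makes the point conditional. It does not remove it. The article does state a rule for categorical outcomes, an embryo-level rate fits that rule naturally, and the rule is anti-conservative there. The same text permits one valid and one invalid analysis.

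Three further readings go too far:
- *A false claim of better embryo quality is likely.* On the assumptions used, a two-sided false positive occurs 11% to 31% of the time. About half of these, 5.5% to 15.4%, would favour the new protocol, against a nominal 2.5%. That is inflated, but not likely. Nor does the article itself claim that LH level affects embryo quality.
- *Clinical pregnancy rate has the same fault.* That would hold only if it were counted per transfer, and the article does not say that it is.
- *The trial's main conclusion is at risk.* It is not. That conclusion rests on cumulative ongoing pregnancy from one aspiration cycle. The Abstract's list of secondary outcomes does not even include high-quality embryo rate.

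**Conclusion.** The point holds in conditional form. The outcome is defined per embryo, women are randomised, and the stated rule for categorical data ignores within-woman correlation. If that rule is applied to pooled embryos, the type I error is about 11% to 31% instead of 5%, and the CI should be 1.2 to 1.9 times wider. These figures rest on an assumed 6 to 10 embryos per woman and an assumed correlation of 0.1 to 0.3, so they illustrate the size and are not properties of this trial. Any positive within-woman correlation gives an error in the same direction. One secondary outcome is affected. The change is worth making because it is nearly free, and it should be made before the data are analysed.

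**What to change.** State the denominator of high-quality embryo rate, and state that it is analysed with the woman as the unit. Name one of these two methods in advance:
- each woman's own proportion, compared between arms under the plan's existing t-test or Mann-Whitney rule; or
- a binomial GEE or logistic model on embryos, with variance clustered on woman.

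The choice should be fixed beforehand because the two weight women differently: the first counts each woman equally, while the second can give more weight to women with more embryos. With the first method, also say how women without an embryo to grade are handled, since their proportion is undefined.

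The cost is a sentence or two of analysis wording and at most one extra model. No new data are needed, and the primary test and sample size stay as they are. The downside is a wider CI for this outcome, which is the correct one.
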